### 2.2. Participants

The study sample will be composed of children aged between 6 and 10 years, all of whom are to be active members of an athletics club located in the district of Leiria, Portugal. All the participants will be affiliated with the Portuguese Athletics Federation and covered by sports insurance, which includes protections regarding training sessions and data collection procedures. The selected age range fits into middle childhood, which is a critical period for motor development and the acquisition of fundamental motor skills. This age range aligns with previous research utilizing the KTK3+ battery, which has been validated and normed specifically for children within this developmental window [24,25], and was chosen because children between 6 and 10 years old are typically enrolled in primary school, where structured physical education and motor skill interventions are most effective at promoting motor competence and physical literacy [26,27]. To be eligible for inclusion in the study, the participants must meet the following criteria: (i) be aged between 6 and 10 years; (ii) be officially registered in the Portuguese Athletics Federation; and (iii) provide written informed consent signed by their legal guardians, along with the child’s verbal assent. The exclusion criteria are as follows: (i) any diagnosed physical or intellectual disability; (ii) any medical contraindications to physical exercise; (iii) failure to obtain parental consent; (iv) failure to complete the entire assessment protocol; (v) failure to complete a minimum of 80% attendance at training sessions in general and, in IG_B, failure to also complete a minimum of 80% attendance at complementary motor activities training sessions; and (vi) being outside the stipulated age range. The children meeting all the eligibility criteria will be randomly assigned to one of the two intervention groups, as described in the study design: (i) Intervention Group A (IG_A) or (ii) Intervention Group B (IG_B).

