## 1. Introduction

Physical activity (PA) is widely recognized as a protective factor against a range of chronic diseases, including cardiovascular conditions, type 2 diabetes, and childhood obesity [1], and contributes to the short- and long-term improvement of the bone, muscle, and psychological health of children and adolescents [2]. Beyond its physiological benefits, PA plays a central role in the development of motor competence (MC) [1], an essential component of children’s physical literacy and a critical predictor of sustained engagement in an active lifestyle throughout life [3,4], and is related to performance in various sports [5].

MC can be defined as the ability to efficiently perform a broad repertoire of fundamental movement skills (FMSs), such as locomotor, stability, and object-control tasks [6,7]. The development of these skills is influenced by the dynamic interaction among individual (e.g., biological and hereditary), environmental (e.g., socio-cultural factors and prior experience), and task-specific factors (e.g., cognitive demand and mechanical properties) [6,8].

The evidence suggests that children with low levels of MC are more likely to show reduced PA participation, poorer physical fitness, and difficulties acquiring more complex movement skills [9,10,11]. These findings highlight the importance of early interventions, particularly during sensitive periods of motor development, when children are most responsive to motor learning through structured programs or educational strategies [12,13].

Structured interventions, such as guided motor games, quality physical education programs, and organized sports such as athletics, may be especially effective in promoting MC, as they provide diverse motor experiences and challenging FMSs. According to Lopes et al. [14], these improvements can positively affect overall physical fitness, which directly impacts cardiovascular health, body composition, and functional capacity. However, the literature lacks conclusive evidence regarding the specific effects of athletics-based programs on MC compared to multilateral or general physical education approaches [15].

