## 2. Materials and Methods

### 2.1. Study Design

This study follows a randomized, controlled experimental design with parallel groups (1:1 allocation ratio), aimed at evaluating and comparing the effects of two types of training protocols on MC in children aged 6 to 10 years. This methodology is used considering the conclusions of the systematic review and the fact that the main researcher is an athletics coach.

The participants will be ecologically assigned into one of two intervention groups, depending upon the training schedule chosen by their parents, according to their availabilities, and being given no prior indication of which of the two programs will function on which schedule: (i) Intervention Group A (IG_A) will receive athletics-based training exclusively, three times per week for 12 consecutive weeks, with each session lasting 60 min; and (ii) Intervention Group B (IG_B) will receive a combined program consisting of athletics-based training twice per week and one additional session per week involving a complementary activity (gymnastics, handball, or motor games), also over 12 weeks and with 60 min sessions.

All the participants will undergo MC assessments at two times: (i) at baseline (T0), prior to the beginning of the intervention; and (ii) at post-intervention (T1), immediately following the 12-week training period.

The post-intervention evaluations will take place three days after the final training session, always in the afternoon, to ensure consistency in the testing conditions. Figure 1 illustrates the participant flow and intervention timeline for the trial.

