### 2.4. Instruments and Procedures

#### 2.4.1. Procedures

The intervention study was structured into several sequential phases to ensure methodological rigor and alignment with the study objectives: (i) SR—A comprehensive literature review was conducted to synthesize the current evidence on the effects of PA, organized sports, and structured training programs on MC in children; (ii) Program Design—the training protocol was developed based on the findings of the SR, incorporating best practices and evidence-based guidelines targeting fundamental motor skill development; (iii) Program Promotion—communication strategies will be employed to inform and engage the stakeholders, including the parents, coaches, and athletics club, about the program’s purpose and benefits; (iv) Definition of Procedures and Objectives—clear operational procedures and objectives for the intervention will be established to ensure fidelity in implementation and alignment with the research aims; (v) Participant Selection and Group Allocation—the sample will be defined, and the participants will be randomly assigned to either the athletics training group (IG_A) or the athletics training plus multi-activity group (IG_B); (vi) Baseline Assessment (T0)—an initial assessment will be conducted to establish the participants’ pre-intervention motor competence and anthropometric measures; (vii) Program Implementation—the 12-week training program will be administered to both intervention groups under controlled conditions; (viii) Post-Intervention Assessment (T1)—a final evaluation will be conducted 12 weeks later to assess the changes and outcomes related to the intervention; and (ix) Data Analysis and Interpretation—the collected data will be statistically analyzed to determine the effectiveness of the intervention, followed by a discussion and formulation of conclusions.

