### 2.5. Study Protocol

The protocol for both groups will be conducted according to the SR [35]. The subjects will be familiarized with the different exercises and tests during the preceding training period. The body composition and MC parameters will also be assessed at baseline (pretest) and post-intervention.

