##### Intervention Group B (IG_B) Training Program

Intervention Group B (IG_B) will be engaged in three weekly training sessions, each lasting 60 min. The sessions will take place at the Municipal Stadium of Leiria—[name]—on Tuesdays and Thursdays from 18:30 to 19:30, and on Saturdays from 10:00 to 11:00. This group will follow a blended training approach: (i) two sessions per week (Tuesdays and Saturdays) focused on athletics, replicating the exact training content as IG_A; (ii) one weekly session (Thursdays) dedicated to complementary motor activities, alternating between gymnastics, handball, swimming, and motor games. The complementary session is strategically scheduled for Thursdays, a day with normally higher attendance and positioned between the two athletics sessions, to ensure optimal participation and recovery. A detailed breakdown of the 12-week program is provided in Table 2.

*Training Objectives*

The IG_B program is designed to evaluate the impact of combined athletics and multi-sport exposure on motor competence development. This group will receive the same foundational athletics training as IG_A, but with an added component of diversified motor experiences. The goal is to determine whether this combined training model will provide greater MC benefits than an athletics-only approach.

*Complementary Activities*

*Gymnastics and handball*

These sessions will emphasize foundational movement skills (FMSs) rather than technical sport-specific mastery. The intent is to expose participants to a variety of motor patterns through basic posture, balance, coordination, object manipulation, jumping, and rolling tasks. In handball, an emphasis will be placed on ball handling, passing, receiving, and spatial awareness, helping to enrich motor diversity.

*Swimming*

In week 10, swimming will be introduced to develop aquatic motor skills, including propulsion and object manipulation in water. This aims to broaden the scope of physical literacy and neuromuscular adaptation through exposure to aquatic environments.

*Motor games*

Motor games will be employed to stimulate key motor competencies, such as locomotion, coordination, balance, and object manipulation. These games are intentionally chosen for their educational value and children’s familiarity with them, ensuring engagement and effective skill acquisition. Activities will include cooperative games, relay formats, object transport tasks, and dynamic obstacle circuits.

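### Training history is not among the listed baseline measures and has no term in the planned model, although groups are formed by parents' choice of schedule, so the difference in gain may be confounded in an unknown direction

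*Protocol article*

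**What the plan says.** **Who is eligible.** Section 2.2 describes the sample as children "all of whom are to be active members of an athletics club". The only sport-related inclusion criterion is to "be officially registered in the Portuguese Athletics Federation". None of the six exclusion criteria concerns years, frequency or level of earlier training.

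**What drives the outcome.** The Introduction lists among the influences on skill development "environmental (e.g., socio-cultural factors and prior experience".

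**What is measured at T0.** Section 2.4.1 describes the baseline assessment as establishing "pre-intervention motor competence and anthropometric measures". Section 2.4.3 covers height, weight and BMI, section 2.5 adds body composition, and section 2.5.1 adds attendance during the programme. Training history appears in none of these.

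**How groups are formed.** Section 2.1 assigns children "depending upon the training schedule chosen by their parents", without telling parents which programme runs in which slot. The same section calls the design randomized, section 2.2 says eligible children "will be randomly assigned to one of the two intervention groups", and section 2.4.1 repeats this.

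**How the groups are compared.** Section 4 plans a 2 (groups) × 2 (time points) ANOVA-RM. It names no covariate and no stratification factor.

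**The concern.** With two time points, the group-by-time test compares mean 12-week gains. It removes a stable difference in level between the groups, but not a difference in how fast the children improve. A child new to athletics may improve at a different rate from one who has trained for several seasons, whichever programme they receive. The age and sex norms behind the quotient do not allow for this.

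Had children been allocated at random, training history would be balanced on average. The only allocation mechanism the article describes is parental choice of schedule, so that balance cannot be assumed. Keeping parents unaware of which programme runs when prevents choice by programme. It does not prevent choice by family routine or availability, which may be related to how long a child has been in the club.

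If the slots differ in this respect, part of the difference in gain between IG_B and IG_A belongs to the mix of children. That part could create an apparent benefit of IG_B or hide a real one. The Discussion intends to encourage clubs to adopt the complementary activities, and to support policy recommendations, if IG_B proves superior. Unless training history is captured at the start, neither analysts nor readers could examine this explanation.

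**Working it through.** The documents give no figure for this bias, so there is nothing of the plan's own to reproduce. What follows shows a range under stated assumptions. It does not estimate what will happen.

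**Inputs from the plan (section 4)**
- 18 children per group, taken as stated
- correlation between T0 and T1 of 0.50
- α = 0.05

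**Assumptions not given in the documents**
- SD of the GMQ: 15
- Extra 12-week gain of newcomers, *g*: 0.25 to 0.75 SD of gain
- Difference in newcomer share between slots, *d*: 20 to 60 percentage points

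**Step 1. SD of the gain.** 15 × √(2 × (1 − 0.50)) = 15 × √1 = 15 points.

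**Step 2. Spurious difference in mean gain, in SD of gain.** Bias = *g* × *d*. Smallest: 0.25 × 0.20 = 0.05. Largest: 0.75 × 0.60 = 0.45.

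**Step 3. Rejection rate with no programme effect.** In a 2 × 2 design the interaction test is equivalent to a two-sided t test on gains, here with 2 × 18 − 2 = 34 degrees of freedom and critical value 2.032. The noncentrality is bias × √(18/2) = bias × 3.

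| *g* (SD) | *d* | Bias (SD) | Bias (GMQ points) | Noncentrality | Rejection rate |
|---|---|---|---|---|---|
| 0.25 | 0.20 | 0.05 | 0.75 | 0.15 | 5.2% |
| 0.50 | 0.20 | 0.10 | 1.50 | 0.30 | 6.0% |
| 0.50 | 0.40 | 0.20 | 3.00 | 0.60 | 9.0% |
| 0.50 | 0.60 | 0.30 | 4.50 | 0.90 | 14.1% |
| 0.75 | 0.60 | 0.45 | 6.75 | 1.35 | 25.9% |

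The rejection rates depend only on the bias in SD units and on the group size. The assumed SD of 15 serves only to convert the bias to GMQ points. At the low end the error rate is practically unchanged. The 26% needs both assumptions at their upper limits.

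**The case against.** Several points on the other side are sound.

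- **The article is condensed.** A reader might infer that training history is never recorded. The documents do not support that. Federation registration is an eligibility criterion, so some registration record must be checked, and a fuller protocol may hold more. What can be said is that the article describes its T0 measures and training history is not among them.
- **Complete beginners may be few.** Children must be active, federated members, and section 2.5 says "The subjects will be familiarized with the different exercises and tests during the preceding training period". Some training therefore precedes T0. This narrows the contrast between newcomers and established members, but it sets no minimum history and documents none.
- **The link between history and slot is not shown.** The IG_B section calls Thursday "a day with normally higher attendance", and a reader might infer that established members hold a habitual slot. Both groups train on Tuesday, Thursday and Saturday, one hour apart, so a remark about a weekday says nothing about who uses which hour. Nor do the documents describe the club's usual training, so one cannot claim that IG_A changes little for established members.
- **Chance imbalance is not bias.** A reader might argue that, in groups this small, shares of newcomers would often differ by chance alone. If slot choice were unrelated to history, that would be ordinary sampling variation, already covered by the 5% error rate. The concern rests on systematic differences between self-selected slots.
- **Allocation is the root cause.** Genuine randomization would remove the systematic part, and other unmeasured factors could be argued in the same way. This is true, but while slot choice stands, a factor the protocol itself names as influential is a reasonable one to record.

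After these points there remains an unlisted variable, a non-random mechanism and an unadjusted model.

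**Conclusion.** The concern holds as a possibility of confounding, with direction and size unknown. Eligibility ignores training history, the article does not list it among the T0 measures, the described allocation does not balance it, and the planned model has no term for it. Two conditions must both hold for the comparison to be distorted: the slots differ in training history, and newcomers gain at a different rate. The documents establish neither.

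If both hold, the spurious difference is 0.05 to 0.45 SD of gain (0.75 to 6.75 GMQ points if the SD is 15), and the nominal 5% test rejects 5.2% to 26% of the time without a programme effect. These figures rest on the assumed newcomer gains and shares.

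A reader might go further and want IG_B superiority claimed only if the adjusted estimate supports it. That does not follow. With about 36 children and a simple proxy for experience, such a rule is a debatable trade-off. Showing both estimates is enough.

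**What to change.** 1. At T0, record for each child the months of athletics training, or the date of first club or federation registration.
2. Report it by arm in the baseline table.
3. Pre-specify it, together with the T0 score, as a covariate in the IG_B versus IG_A comparison of GMQ, and report the estimate with and without it.
4. Reconcile the statements on allocation. If parental slot choice is kept, describe the result as coming from non-random groups.

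The cost is one data field, from club or federation records or one question to parents at consent, and one degree of freedom for the history term in an analysis of about 36 children. No additional children, staff or tests are needed. A single linear term may not capture fast early gains fully, and adjustment does not replace randomization, but it lets readers see whether the groups differ and how far the estimate moves. If training history is not captured at T0, its later recovery is uncertain and any adjustment would be post hoc.

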#### 2.5.1. Training Programs

The training programs will be implemented in both groups over 12 consecutive weeks, with 60 min training sessions three times a week, at Leiria’s Main Stadium, [name]. The coaches will monitor the children’s attendance and absences at the training sessions, recording them on a specific attendance sheet.

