## 4. Statistical Analysis

The required sample size was calculated using the G*Power software (3.1.9.4; Heinrich Heine University Düsseldorf, DE). As the aim is to detect differences in the KTK3+ between the two groups, and considering that the analysis will be performed on the outcomes, a between–within ANOVA-RM (2 [groups] × 2 [time points]) will be conducted, anticipating a ‘large’ effect size (f = 0.4) based on similar previous studies using the KTK3+ [26,27,36], with an α = 0.05, a statistical power of (1 − β) = 0.95, correlated dependent variables with an r = 0.50, and a violation of sphericity (ε) = 0.80. This analysis will require a total sample size of 18 individuals per group. Thus, the study should start with an additional 15% of the planned sample size for each group to account for potential dropouts as suggested by several authors (e.g., [37]). It will also be comparable to previous school-based MC studies that employed the KTK3+ as an outcome measure in early childhood and primary education contexts [24,25], considered adequate for the study objectives and the planned statistical analyses. The means and standard deviation will be calculated for all the studied variables. The normality and homoscedasticity will be verified with the Shapiro–Wilk (n < 50) and Levene’s tests, respectively. The statistical analyses will be conducted in IBM SPSS Statistics version 27. The referred to ANOVA-RM will be applied to each of the four KTK3+ battery tests independently and to the KTK3+ battery results as a whole, namely to its raw results and to its Global Motor Quotient. Thus, we will be conducting six distinct analyses and will extract conclusions from each of them, with the latter two being the most important, as global results. Nevertheless, if specificities can be found for the other four, we intend to address and to consider them.

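### Two exclusion criteria act after allocation, and one sets an extra attendance threshold in IG_B only, so the planned comparison is of adherent completers selected by unequal rules

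*Protocol article*

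**What the plan says.** Protocol article, section 2.2 (Participants), lists among its exclusion criteria (iv) "failure to complete the entire assessment protocol" and (v) "failure to complete a minimum of 80% attendance at training sessions in general". For one arm, criterion (v) goes further: "in IG_B, failure to also complete a minimum of 80% attendance at complementary motor activities training sessions". The same section then states: "The children meeting all the eligibility criteria will be randomly assigned to one of the two intervention groups".

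Section 2.5.1 sets the programme "over 12 consecutive weeks, with 60 min training sessions three times a week", with coaches recording attendance as it runs. The IG_B programme description has "one weekly session (Thursdays) dedicated to complementary motor activities" and calls Thursday "a day with normally higher attendance". It also says that IG_B's Tuesday and Saturday athletics sessions have the same content as those of IG_A.

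Section 4 plans a 2 × 2 repeated-measures ANOVA on 18 children per group and says "the study should start with an additional 15% of the planned sample size for each group to account for potential dropouts".

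**The concern.** Neither criterion can be checked when children are allocated. Attendance is complete only after week 12. Section 2.4.1 puts allocation (step v) before baseline testing (step vi), so even the T0 half of the testing requirement comes after allocation. The stated order, all criteria met and then assigned, cannot be followed. In practice the two criteria delete children from groups already formed.

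The deletion rule also differs by arm. Thursday content is what separates the two programmes, and only IG_B has a Thursday threshold. IG_B is thus filtered on uptake of the component under test, and IG_A has no counterpart. Any difference found would describe children who kept attending. The Discussion wants to use the result to encourage clubs to adopt the activities, which is a decision about every child offered them.

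If excluded children are not tested at T1, the effect of removing them cannot be estimated later.

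**Working it through.** **Thresholds.** Sessions per child: 12 weeks × 3 = 36. Complementary sessions in IG_B: 12 × 1 = 12.
- Overall rule, both arms: 0.80 × 36 = 28.8, so at least 29 of 36.
- Extra rule, IG_B only: 0.80 × 12 = 9.6, so at least 10 of 12.

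**Same register, different fate (no attendance assumption needed).** A child misses three Thursdays and nothing else: 33/36 = 92% overall, 9/12 = 75% on Thursdays. In IG_A the child stays; in IG_B the child is removed. An IG_A child could miss seven Thursdays and stay (36 − 7 = 29).

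**Starting numbers.** The plan's 18 per group plus 15% is 18 × 1.15 = 20.7, so 21 per group. The 18 itself does not reproduce. With f = 0.4, r = 0.50, ε = 0.80, α = 0.05 and power 0.95, the interaction test has λ = f²·N·m·ε/(1 − r). At N = 28 this is 0.16 × 28 × 2 × 0.8/0.5 = 14.3, with power 0.961, so 14 per group suffice. That is a separate matter; 18 is used below only as the plan's own target.

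**Retention.** The documents give no attendance rate, so the per-session probabilities are assumptions, the same in both arms. Let T ~ Bin(12, p_T) be Thursday attendances and O ~ Bin(24, p_O) the others.
- IG_A kept: P(T + O ≥ 29).
- IG_B kept: Σ over c = 10, 11, 12 of P(T = c) × P(O ≥ 29 − c).

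| Thursday | Other days | IG_A kept | IG_B kept | Gap (points) | Of 21: IG_A / IG_B |
|---|---|---|---|---|---|
| 0.85 | 0.85 | 83.8% | 67.5% | 16.3 | 17.6 / 14.2 |
| 0.90 | 0.90 | 97.6% | 87.9% | 9.7 | 20.5 / 18.5 |
| 0.95 | 0.95 | about 100% | 98.0% | 1.9 | 21.0 / 20.6 |
| 0.90 | 0.85 | 90.3% | 83.0% | 7.3 | 19.0 / 17.4 |
| 0.95 | 0.85 | 95.0% | 93.6% | 1.3 | 19.9 / 19.7 |

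If attendance propensity varies between children (beta-binomial, mean 0.85 to 0.95), the gap is about 2 to 10 points.

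**Possible bias in mean change, two scenarios.**
- *One general attendance trait.* In the beta-binomial model with mean 0.85 or 0.90, children kept in IG_B average about 0.05 to 0.08 SD higher on the latent trait than those kept in IG_A. If the trait correlates 0.2 to 0.4 with gain, the shift is between 0.2 × 0.05 = 0.01 and 0.4 × 0.08 = 0.03 SD of change.
- *Extreme.* If the extra share q removed from IG_B were exactly the lowest gainers, the mean of those left rises by φ(z_q)/(1 − q). For q = 0.10: 0.1755/0.90 = 0.19 SD. For q = 0.16: 0.2433/0.84 = 0.29 SD. If they were the highest gainers, the same shift would occur with the opposite sign. (Here q is a share of all starters. Taken as a share of those who pass the overall rule, 0.163/0.838 = 0.19, the upper figure is about 0.34 SD.)

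**The case against.** **Direction.** Because IG_B is the arm expected to win, a reader might infer that the rule favours it: children who dislike or struggle with the new activities leave IG_B's data while similar children stay in IG_A's. The documents do not support this. Nothing in them says why sessions are missed. Illness or transport would be neutral, and children absent for another sport could be strong movers, which would push the other way. The objection stands: unequal selection is shown, its direction is not.

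**Size.** Equal attendance on all days gives the widest gaps, whereas the protocol itself expects better attendance on Thursdays. At 0.95 on Thursdays and 0.85 otherwise the gap is about one point. This also stands, with the caveat that a habit formed under athletics training may not carry over to new activities. The 0.2 to 0.3 SD figure is an extreme and not an estimate.

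**Power.** A reader might infer that the trial will end up underpowered. IG_B falls below 18 of 21 only under the lower assumed rates, and the stated inputs need only 14 per group for the interaction test. Loss of power is not established.

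**An unseen analysis plan.** A condensed article may leave analysis sets to a fuller document, so the lack of a stated all-allocated analysis would be no fault in itself. This does not answer the point. The article does more than stay silent: it makes these events exclusion criteria and makes one of them specific to an arm.

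**Allocation.** Section 2.1 assigns children by the schedule their parents choose, while sections 2.2 and 2.4.1 say random. Analysing everyone as allocated would not by itself secure randomised comparability. True, but that gives no reason to add a second source of imbalance.

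**Conclusion.** The point holds as a defect in the analysis population and should be corrected before T1. Two exclusion criteria depend on events after allocation. One applies a stricter test in IG_B alone, on the component that distinguishes the arms. This follows from the text and the session counts, without any assumption about attendance.

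The consequences do rest on assumptions. With attendance of 0.85 to 0.95, and Thursdays no worse than other days, IG_B retention is about 1 to 16 percentage points below that of IG_A. The bias in KTK3+ change is of unknown sign. It is negligible if absence reflects one general trait, and could reach a few tenths of an SD only if the extra removals were concentrated among the lowest or the highest gainers.

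**What to change.** 1. Delete (iv) and (v) from the exclusion criteria, leaving only conditions that can be checked before allocation.
2. Invite every allocated child to T1 whatever their attendance.
3. Make the primary analysis all allocated children in their allocated group. Use a method that does not drop a child with one missing time point, for example a mixed model for repeated measures, which assumes that missingness is explained by the observed data. Use every available KTK3+ task: section 4 analyses the four tasks separately, so one missing task need not cost the child's other task scores.
4. Keep attendance only as a secondary per-protocol analysis with the same two thresholds in both arms: at least 29 of 36 sessions overall and at least 10 of 12 Thursday sessions. The overall threshold alone is not enough, because an IG_B child with all 24 athletics sessions and only 5 complementary ones reaches 29.
5. Report the numbers allocated, tested at T1 and meeting the attendance thresholds, by arm.

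The cost is revised wording and one extra T1 invitation for low attenders. The estimated effect may be slightly diluted, since children who received little of the programme count in full. Training content is unchanged. The contradiction between random and schedule-based allocation is not cured by this and needs its own correction.
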